## Abstract

Supplemental Digital Content is available in the text

## Introduction

1

Risk factors of cardiovascular disease are increasing in China, leading to a continuous increase in the number of cardiovascular disease. According to the “China Cardiovascular Disease Report 2018” released in 2019,^[1]^ the prevalence of coronary heart disease continues to rise. The report estimates that 290 million people suffer from cardiovascular diseases and 11 million people suffer from coronary heart disease. Cardiovascular death accounts for the first cause of death in both urban and rural areas. It is responsible for about 45.50% of deaths in rural areas and 43.16% in urban areas. Since 2012, the mortality rate of coronary heart disease has shown an upward trend, and the rapid increase of acute myocardial infarction (AMI) mortality rate is the main reason. Currently, AMI treatment is percutaneous coronary intervention, but the nosocomial fatality rate of ST-Elevation Myocardial Infarction (STEMI) patients has not decreased significantly due to the obvious delay in the patient's treatment and the low total reperfusion treatment rate.^[2]^ At the same time, the treatment of AMI patients occupies a large proportion of public health resources, which has continued to grow at a rate of 29.15% since 2014. In 2016, the total cost of AMI hospitalization was 19.085 billion yuan.^[3]^ Unstable angina (UA) is a group of clinical angina syndromes that belongs to acute coronary syndrome (ACS), including primary exertional angina, advanced exertional angina, resting angina, post-infarct angina, and variable angina. UA is characterized by a progressive increase in angina symptoms, new episodes of rest or nocturnal angina or an extended duration of angina. Due to the unique pathophysiological mechanism and clinical prognosis of UA, patients may develop AMI if not properly treated on time.^[4]^ Treatment of UA has a positive effect on reducing AMI episodes. Since it is difficult to distinguish between UA and NSTEMI, treatment guidelines have unified diagnosis and treatment.^[5]^ In clinical practice, the treatment of UA is usually aimed at solving patients’ current symptoms, which are prone to relapse or even worsen after discharge.

Unstable angina pectoris belongs to the categories of “Xiongbi” and “Xintong” in Chinese medicine. Chinese medicine has a long history in the treatment of heart disease, and there are rich theoretical knowledge and prescriptions regarding the same.^[6–8]^ A study analyzed the syndrome elements of 411 patients with unstable angina pectoris in six hospitals in Beijing, Hubei, and Henan. The results showed that blood stasis accounted for the largest proportion (72.7%), followed by qi deficiency and phlegm turbidity, which accounted for 48.4% and 22.9%, respectively.^[9]^ Stagnation of phlegm and blood stasis are the main symptoms of unstable angina pectoris.^[10–13]^ As a TCM compound, GLDS are composed of *Trichosanthis fructus* such as *Allii macrostemonis bulbus*, *Salviae miltiorrhizae*, *Amomi fructus*, and *Dalbergiae odoriferae lignum*. Previous clinical studies^[14–16]^ showed that GLDS have good clinical efficacy in treating unstable angina pectoris of phlegm-blood stasis type, with the total effective rate as high as 86.2%. GLDS were derived from the famous veteran Chinese medicine of Guang’anmen Hospital combined with the ancient prescriptions and clinical experience of TCM. They were used to treat unstable angina pectoris of coronary heart disease with phlegm and blood stasis syndrome by promoting blood circulation and resolving phlegm method of TCM. GLDS have been used in clinical practice of TCM for more than 60 years, which is also accepted by most Chinese patients. Nevertheless, the clinical safety and efficacy of GLDS in the treatment of unstable angina pectoris patients with phlegm-blood stasis syndrome still lacks accurate verification.

## Methods and analysis

2

### Objective

2.1

The objective of this randomized, controlled, double-blind trial is to assess the effectiveness and safety of GLDS in the treatment of unstable angina pectoris.

### Trial design

2.2

Funders will not be involved at any point during the entire process, including research design, data collection, analysis and interpretation, and manuscript writing. Sixty patients will participate in this trial at the Guang’anmen Hospital of the Chinese Academy of Medical Sciences in accordance with the established inclusion and exclusion criteria. All the information about the study will be fully explained to the subjects by the researchers, and the subjects will sign an informed consent from before participation in the study. Any information and privacy of participants will be kept strictly confidential. The conduct of the trial and patient safety will be monitored by an independent data and safety monitoring committee, monitored according to established guidelines and stopped as necessary. The study design is summarized in Figure 1.

**Figure 1 F1:**
[figure not shown]
GLDS = Gualou Danshen granules.

### Registration

2.3

Declaration of Helsinki^[17]^ and Good Clinical Practice (GCP)^[18]^ were the reference criteria for developing this study protocol. The trial has been approved by Research Ethics Committee of the aforementioned hospitals (No.2019-187-KY-01) and registered at chictr.org (registration number ChiCTR2000031780).

### Recruitment of participants

2.4

The trial will recruit patients with two strategies. One is to put up posters on hospital bulletin boards. The contents include suitable conditions for patients, unsuitable people, the anticipated place and time of treatment, and the contact information of test operators. The other is to recruit outpatient patients in the hospital, through seeking the consent of patients who meet the trial standards, to further complete the recruitment of test patients.

### Diagnostic criteria

2.5

The criteria for the diagnosis of unstable angina pectoris in this trial were formulated according to the Guidelines for the Diagnosis and Treatment of Unstable Angina Pectoris and Non-ST Segment Elevation Myocardial Infarction (2007)^[4]^ issued by the Cardiovascular Branch of the Chinese Medical Association. The diagnostic criteria of blood stasis of heart and phlegm obstruction of heart refer to Guiding Principles of Clinical Research on New Chinese Medicines in 2002.^[19]^

### Inclusion criteria

2.6

1.Conforms to the diagnostic criteria of unstable angina pectoris, set out in the guidelines for the diagnosis and treatment of unstable angina pectoris and non-ST-segment elevation myocardial infarction published by the Chinese society of cardiovascular diseases. The diagnostic criteria of TCM syndromes are consistent with phlegm and blood stasis obstruction syndrome.2.Patients with coronary heart disease confirmed by coronary angiography (1 or more major coronary artery stenosis degree ≥ 50%).3.Aged 35 to 75 years.4.Voluntary participation in this clinical study and signed informed consent form. Subjects must take the medicine for 4 weeks, complete the scale and test before and after treatment. A fixed contact way to complete the follow-up work is also requisite.

### Exclusion criteria

2.7

1.Those who have been confirmed to have chest pain caused by stable angina pectoris, AMI, aortic dissection, other congenital heart disease, valvular disease, severe neurosis, etc.2.Poorly controlled hypertension (systolic blood pressure ≥160 mm Hg or diastolic blood pressure ≥100 mm Hg), severe cardiopulmonary dysfunction (heart function level III or IV).3.Chest tightness and pain caused by arrhythmia.4.Acute stage of cerebral infarction.5.Patients with severe primary diseases such as liver, kidney, or hematopoietic system disease, or liver function ALT or AST value > 1.5 times the upper limit of normal value, or those with abnormal renal function.6.Those with an acute infection within the last 2 weeks.7.Those with other serious diseases that must be treated (such as blood diseases, tumors, etc).8.Diabetes that does not meet the general control standards, or if more serious diabetes complications occur.9.Women who are pregnant or breastfeeding.10.Those with known allergies or allergies to the test drug ingredients.

In addition,

1.patients who are participating in other clinical trials or patients whose clinical trials finished less than 1 month ago will be excluded;2.if researchers believe that there are other reasons rendering the subject unsuitable for clinical trials.

### Randomization and blinding

2.8

The randomized grouping method will be used by the clinical evaluation center of the Chinese Academy of Medical Sciences. Random grouping tables will be generated by SAS 6.12 statistical software. The sixty eligible participants will be assigned to either the GLDS group or placebo group in a ratio of 1:1. All drugs will be labeled by pharmaceutical companies according to the random grouping table. Double blindness will be guaranteed during the whole experiment. Random grouping numbers will be stored in opaque sealed envelopes until the end of the experiment or an emergency occurs.

### Sample size estimation

2.9

According to the calculation formula of sample size, the total effective rate of GLDS is 86.2% in combination with previous clinical study information. Consequently, the test set *a* = 0.05, beta = 0.10, *f* (*a*, beta) = 10.5, using a unilateral test, the initial estimated sample number was 27.5, and the integer number was 28. According to the test funds and other related issues, the drop-out rate was limited to <5%. The number of cases in each group was set at 30, and the total number of cases in two groups at 60.

### Intervention

2.10

The loading test method will be used. Both groups will be treated with routine western medicine. The routine western medicine treatment is strictly in accordance with the “Guidelines for the Management of Unstable Angina Pectoris-Non-ST Segment Elevation Myocardial Infarction 2012ACCF/AHA.” The experimental group will be given GLDS, 6 g, three times a day. The control group will be given placebo granules, 6 g, three times a day. The placebo is mainly composed of starch, which ensures that the shape and odor of the placebo granules are the same as those of the GLDS. The course of treatment was set for 4 weeks, during which no other Chinese patent medicine or decoction was used to treat coronary heart disease.

### Outcomes

2.11

Incomplete data will affect the judgment of efficacy and safety, so it can only be adopted when the data integrity is over than 80%, data that does not meet this requirement will be excluded. The data collected will be the following:

1.Clinical Symptom Rating Scale (supplementary file 1);2.Phlegm-Blood Stasis Syndrome Scale (supplementary file 2);3.Seattle Angina Questionnaire (supplementary file 3);4.Chinese medicine syndrome efficacy evaluation criteria in accordance with the Guidance of Clinical Research on New Chinese Medicine for Coronary Heart Disease Angina Pectoris issued by the Ministry of Health of the People's Republic of China in 2002.

The efficacy calculation is as follows: Curative effect index (n) = (pre-test integral-post-test integral)/pre-test integral × 100%. Effectiveness is defined as: significant effect: the clinical symptoms and signs were significantly improved, and the integral of TCM syndromes was reduced by more than 70%. Effective: The clinical symptoms and signs were improved, and the integral of TCM syndromes was reduced by more than 30%, <70%. Invalidity: Clinical symptoms and signs did not improve significantly, or even worsened, the TCM syndrome score decreased by less than 30%. Aggravation: clinical symptoms and signs were aggravated, and the integral of TCM syndromes decreased <0.

All the scales will be completed on the day of registration and after taking the medicine for 4 weeks. We will compare the index changes before and after taking the drug and perform data collation for statistical analysis in order to evaluate the effectiveness of GLDS in the treatment of unstable angina pectoris.

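### The 80% completeness rule in section 2.11 takes patients without a week-4 assessment out of the effectiveness comparison, which can bias it

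*Protocol article*

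**What the plan says.** Section 2.11 opens with a reason, "Incomplete data will affect the judgment of efficacy and safety", and follows it with a rule: "it can only be adopted when the data integrity is over than 80%, data that does not meet this requirement will be excluded". It does not define data integrity or say whether the 80% is counted per patient, per scale or per item.

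The same section fixes two assessment times: "All the scales will be completed on the day of registration and after taking the medicine for 4 weeks". The curative effect index is the change from the score before treatment to the score after it, divided by the score before.

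Three other places bear on the point:
- Section 2.8 (Randomization and blinding): "The sixty eligible participants will be assigned to either the GLDS group or placebo group in a ratio of 1:1".
- Section 2.9 (Sample size estimation) plans for few losses: "the drop-out rate was limited to <5" per cent.
- Section 2.6 (Inclusion criteria), criterion 4: "Subjects must take the medicine for 4 weeks, complete the scale and test before and after treatment".

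Section 2.12 (Safety and adverse events) commits to following and reporting every adverse event and attaches no completeness condition.

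**The concern.** Completeness at week 4 is known only after allocation. It can depend on the assigned arm, on whether the patient improved, and on how well the granules were tolerated. A rule that keeps or discards data on that basis can leave two groups that differ in ways randomisation did not produce.

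The outcome definition sharpens the problem. Section 2.11 has categories for patients who do not improve or who get worse, so failures are meant to count. A patient who worsens and has no week-4 scales would be left out instead of being counted as a failure. If one arm loses more such patients, its effective rate rises without any drug effect. With 30 patients per arm, one or two exclusions already move a rate by several points.

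**Working it through.** **1. The plan's own allowance for losses.** Section 2.9 rounds 27.5 to 28 per group and sets 30. With 5% drop-out, 28/0.95 = 29.5, rounded up to 30, so this step reproduces. Below 5% of 60 means fewer than 3 patients, so at most 2. This is a planning figure. Nothing in the article ties the 80% rule to it or limits exclusions to it.

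**2. What the rule does to a patient with no week-4 scales.** There are two assessment times with the same scales at each, so the share of scale data present is 1/2 = 50%, below 80%.
- Per patient: 50% of the scale data, excluded.
- Per scale: each scale is 50% complete, excluded.

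**3. What it does to a partly completed week 4.** With a complete baseline and a share x of the week-4 items, counted with equal weight, passing requires (1 + x)/2 > 0.80, so x > 0.60. A patient with 60% or fewer of the week-4 items is also excluded, although some outcome data exist.

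**4. Effect on an observed rate.** Assume 18/30 = 60.0% responders in each arm, with only non-responders removed, and from one arm only. The formula is 18/(30 − k).

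| Removed, k | Observed rate | Shift (points) |
|---|---|---|
| 1 | 18/29 = 62.1% | +2.1 |
| 2 | 18/28 = 64.3% | +4.3 |
| 3 | 18/27 = 66.7% | +6.7 |
| 5 | 18/25 = 72.0% | +12.0 |

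The rows k = 1 and k = 2 fit within the planned drop-out; k = 3 and k = 5 exceed it. If 2 non-responders are lost from each arm, both rates are 64.3% and the difference stays zero.

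**5. Effect on the false-positive rate.** Simulation with 30 per arm, a true rate of 70% in both arms, a pooled z test and 400,000 runs. A share q of GLDS non-responders is removed and nobody else. The expected GLDS rate is 0.70/(0.70 + 0.30(1 − q)).

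| q | Share of GLDS arm removed | Expected GLDS rate | One-sided error | Two-sided error |
|---|---|---|---|---|
| 0 | 0% | 70.0% | 0.050 | 0.049 |
| 10% | 3% | 72.2% | 0.073 | 0.055 |
| 20% | 6% | 74.5% | 0.104 | 0.067 |
| 40% | 12% | 79.5% | 0.205 | 0.127 |

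**6. One result that changes sides.** Suppose 22/30 respond on GLDS and 15/30 on placebo. The two-sided p-value is 0.063 (uncorrected chi-square) or 0.110 (Fisher). Removing 2 GLDS non-responders gives 22/28 against 15/30, with p = 0.024 or 0.031. Two of 60 is 3.3%, within the planned drop-out.

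**The case against.** **The rule adds little, because the index needs a post-treatment score.** A patient without week 4 has no curative effect index with or without the 80% sentence, and handling of missing data is commonly left to an analysis plan. In part this stands: the lack of a statement on analysis sets or imputation is not a finding here. But the sentence does more than stay silent. It prescribes exclusion, so an analysis plan that kept these patients would contradict it, and it also discards partly completed week-4 assessments (step 3).

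**The illustrations are one-sided worst cases.** This stands. All removals are non-responders from one arm. Within the planned drop-out, the shift in the 60% example is at most 4.3 points, and equal losses from both arms cancel there.

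A reader might infer stronger claims, which the documents do not support:
- *That the rule expressly drops patients.* The text excludes data and leaves the unit undefined. On a per-scale reading a patient could stay in for other scales. What holds on either reading is that a patient with no week-4 assessment leaves the effectiveness comparison.
- *That adverse-event cases vanish from safety.* Section 2.11 gives safety as part of its reason, but the items it then lists concern efficacy, and section 2.12 has every adverse event followed and reported. The two sections need reconciling; a loss of cases is not shown.
- *That inclusion criterion 4 removes non-completers after allocation.* It stands beside consent and the need for a fixed contact, and reads naturally as a commitment at enrolment.
- *That the bias can be measured against the planned treatment difference.* Section 2.9 gives no control rate. Solving back from 27.5 gives about 48.7% with f = 10.5, or 52.3% with a one-sided f of 8.56. The implied difference is then 86.2 − 48.7 = 37.5 or 86.2 − 52.3 = 33.9 points, an assumption in either case.

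**Conclusion.** The point holds in this form: section 2.11 states an exclusion rule that acts after randomisation and takes every patient without a week-4 assessment out of the effectiveness comparison. It is a rule badly fixed in the current text, not a detail left to another document.

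Bias is possible and its direction is not known in advance. Under the assumed patterns, 1 or 2 one-sided removals shift a 60% rate by 2.1 to 4.3 points, and 5 removals shift it by 12.0 points. Removing 6% of the GLDS arm, all non-responders, roughly doubles the one-sided error in step 5 (0.050 to 0.104). If exclusions are few and unrelated to arm and outcome, the effect would be small.

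These figures rest on assumed response rates and exclusion patterns, since the article gives none, and on completeness being counted over the scale data. A reader might conclude that the comparison is certain to be biased or has ceased to be randomised. The documents do not support that, because they give no information on how many patients will lack week-4 data or why.

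**What to change.** 1. In section 2.11, delete the 80% exclusion as the rule for the main efficacy analysis. State that all randomised patients are analysed in the arm assigned, with a missing-data method fixed before unblinding.
2. For the total effective rate, one workable choice is to count a missing week-4 assessment as not effective, with multiple imputation as a sensitivity analysis. Other prespecified methods would also serve.
3. Keep the over-80%-complete analysis only as a labelled sensitivity analysis, and define there what completeness is counted over.
4. State that the completeness rule does not apply to safety, so that sections 2.11 and 2.12 agree.
5. As a wording note, phrase inclusion criterion 4 as willingness to complete the treatment period and both assessments.

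The cost is protocol wording; the planned 60 patients stand. Response rates may look less favourable, and counting missing as not effective is a conservative convention that should be described as such.

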### Data management and statistical analysis

2.13

The general data, safety indicators and therapeutic effect of angina pectoris are to be observed before and after treatment. SPSS 20.0 statistical software will be used for data analysis. The measurement data will be expressed as mean (+standard deviation). One-way analysis of variance will be used for comparison among multiple groups, and the homogeneity of variance test will be conducted using the Levene method. If the variance is homogeneous, LSD-T test will be used for pair comparison. If the variance is not uniform, the Tamhane method will be used for pair comparison. Non-normally distributed data will be represented by median and quartile, using rank sum test. *P* < .05 will be considered statistically significant.

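### The only power claim rests on a responder rate cut from a before-and-after score; if that rate leads, it costs about 9 points of power at the plan's implied control rate, and more at higher control rates

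*Protocol article*

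**What the plan says.** Three sections of the protocol article bear on this.

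- **2.11 Outcomes.** The syndrome score is taken at registration and after 4 weeks, and efficacy is expressed as "Curative effect index (n) = (pre-test integral-post-test integral)/pre-test integral × 100"%. Cuts at 70%, 30% and 0, combined with a judgement on symptoms and signs, give four ordered grades: significant effect, effective, invalid and aggravation. Three scales are also collected, and the section says that changes in the indexes will be compared.
- **2.9 Sample size estimation.** The one efficacy input is "the total effective rate of GLDS is 86.2% in combination with previous clinical study information". With alpha 0.05, beta 0.10, a multiplier of 10.5 and "using a unilateral test", it reports that "the initial estimated sample number was 27.5, and the integer number was 28". It then sets 30 per group.
- **2.13 Data management and statistical analysis.** Measurement data go to one-way ANOVA with LSD-t or Tamhane comparisons. For the rest, "Non-normally distributed data will be represented by median and quartile, using rank sum test". No test for a proportion is named, and no baseline covariate.

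The article does not define the total effective rate. It is read here as significant effect plus effective.

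**The concern.** On that reading, the outcome used for sizing collapses a score at a 30% reduction. A patient who improves by 31% counts the same as one who improves by 95%, and one at 29% the same as one who worsened. The trial already holds the score and the four grades, so the lost information would cost nothing to keep. Dividing by the baseline score also makes the percentage index unstable when that score is low.

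What is at stake is how well 60 patients are used. The article's own discussion accepts that the number of cases is relatively small. The 90% power claim attaches only to the rate, and both arms receive routine western medicine. If control response were higher than the plan's arithmetic implies, a rate comparison would lose power quickly. The article never says which comparison leads, so a reader cannot tell whether the rate or a score carries the power claim.

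**Working it through.** **Inputs from the document:** GLDS effective rate 86.2%, alpha 0.05, power 90%, multiplier 10.5, 27.5 rounded to 28 and then 30 per group, drop-out below 5% (all 2.9); cut at 30% (2.11).

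**Not in the document:** the control rate, and the mean, SD and baseline correlation of the score.

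**Step 1. The plan's own figure.** The usual formula is n = f × [p1(1−p1) + p2(1−p2)] / (p1−p2)². It cannot be run forward because p2 is missing. Solving for p2 with n = 27.5, f = 10.5 and p1 = 0.862 gives p2 = 0.487. Check: 10.5 × (0.1190 + 0.2498) / 0.1408 = 27.5. Other standard variants, two-sided or one-sided, give p2 between 42.5% and 52.3%. The drop-out step reproduces: 28 / 0.95 = 29.5, hence 30.

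**Step 2. Sidedness.** (1.960 + 1.282)² = 10.5 is the two-sided multiplier. The one-sided value is (1.645 + 1.282)² = 8.56. The text says one-sided but the number is two-sided, so both are shown.

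**Step 3. Link the rate to the score.** Assume the percentage reduction is normal with the same SD in both arms, and that a patient is effective when it passes 30%. The standardised difference is then d = probit(0.862) − probit(p2), with probit(0.862) = 1.089:

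- p2 = 48.7%: d = 1.089 + 0.033 = 1.12
- p2 = 60%: d = 1.089 − 0.253 = 0.84
- p2 = 65%: d = 1.089 − 0.385 = 0.70

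**Step 4. Power with 30 per arm.** For the rate: exact enumeration of the chi-square test (for the one-sided column, its signed root). For the score: t-test with 58 degrees of freedom and noncentrality d × √(30/2).

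| Control rate | Two-sided: rate / score | Gain | One-sided: rate / score | Gain |
|---|---|---|---|---|
| 48.7% (implied) | 90% / 99% | 9 | 95% / 99.6% | 5 |
| 60% (assumed) | 65% / 89% | 24 | 77% / 94% | 17 |
| 65% (assumed) | 49% / 76% | 28 | 63% / 85% | 22 |

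**Step 5. Four grades by rank sum.** In simulation (two-sided, cuts at 0, 30 and 70%), power was about 97 to 98%, 81 to 84% and 67 to 69% at the three control rates. Keeping the four grades therefore recovers most of the loss.

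The score column does not use the baseline as a covariate. ANCOVA would add to it by an amount that depends on the baseline correlation, which the document does not give.

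**The case against.** The strongest reply is that the plan never commits to comparing effective with not effective. The total effective rate appears only as background from earlier studies and as the sizing input. Section 2.11 keeps four grades and says index changes will be compared, and 2.13 names only tests for scores and ranks. Sizing on a conservative binary outcome and then analysing scores would lose no power. This stands: a reader might infer that the plan throws the score away, and the documents do not support that. The loss arises only if the rate leads.

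A reader might also take the 24 to 28 point figures as the plan's loss. They are not. Control rates of 60% and 65% appear nowhere in the article; its own numbers point to about 49%, where the loss is about 9 points, or 5 on the one-sided test named.

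Two further objections stand in part. The grades require improved symptoms and signs as well as the score reduction, so the normal-cut model only approximates the rate, and moving to the score changes somewhat what is measured. And the exact test and covariates are often left to an analysis plan, which is not shown. But 2.13 does name its tests, and none of them uses the baseline score as a covariate.

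**Conclusion.** The point holds in a limited form. The only outcome tied to a power claim is in essence a dichotomised score, the tests named suit scores but ignore baseline as a covariate, and no test is named for the rate that set the size. If the rate leads, the cost is about 9 points of power at the implied control rate (two-sided) or 5 (one-sided). It rises to 24 to 28 points (two-sided) or 17 to 22 (one-sided) only if the control rate were 60% to 65%.

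All of this assumes 30 evaluable patients per arm, a normal score with equal SDs, and a rate that behaves as a pure cut at 30%. The direction does not depend on sidedness; the size does. This is an efficiency weakness with a cheap remedy, and it does not invalidate the trial.

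**What to change.** - **2.11 and 2.13:** compare the arms on the week-4 TCM syndrome score by ANCOVA with the baseline score as covariate, in place of the unadjusted ANOVA and the percentage index.
- **Effective rate:** define it, and report it by arm with a 95% CI for the difference as a secondary summary. If the 2002 grading must lead, compare all four ordered grades with the rank-sum test already named.
- **2.9:** state that the size was set on the effective rate.

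**Cost:** no new patients, visits or measurements, since both scores are already collected. Two downsides should be accepted openly. A mean score difference is less familiar to readers than an effective rate. And because the article names no primary outcome, this change in effect chooses one, so it should be settled before unblinding.

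### The plan names no GLDS-versus-placebo contrast for the scale changes and only unadjusted tests, although every scale has a baseline score; ANCOVA on the week-4 score would cost nothing

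*Protocol article*

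**What the plan says.** Four statements in the protocol article bear on this.

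- **Timing (2.11 Outcomes).** "All the scales will be completed on the day of registration and after taking the medicine for 4 weeks". A baseline and a week-4 value are therefore planned for each scale.
- **How effectiveness is judged (2.11 Outcomes).** "We will compare the index changes before and after taking the drug and perform data collation for statistical analysis", with the aim of evaluating the effectiveness of GLDS. The placebo arm is not mentioned in that sentence.
- **The index (2.11 Outcomes).** "Curative effect index (n) = (pre-test integral-post-test integral)/pre-test integral", as a percentage. The category definitions that follow apply cuts at 0, 30% and 70% to the TCM syndrome score.
- **The tests (2.13 Data management and statistical analysis).** The section opens: "The general data, safety indicators and therapeutic effect of angina pectoris are to be observed before and after treatment". It then gives the methods: "One-way analysis of variance will be used for comparison among multiple groups"; "If the variance is homogeneous, LSD-T test will be used for pair comparison", with the Tamhane method for unequal variances; and "Non-normally distributed data will be represented by median and quartile, using rank sum test". None of these carries a covariate. The section does not say whether the week-4 score, the change or the index enters the test.

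**The concern.** Two things are at stake.

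**Precision.** The trial has 30 patients per arm, and the Discussion concedes that this is relatively small for funding reasons. A test on raw change or on the week-4 score alone leaves unexplained a part of the variance that the baseline score would remove.

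**The meaning of a positive result.** Patients enter with unstable angina (2.6) and both arms receive routine western medicine (2.10). Some improvement in both arms is plausible whatever GLDS does. A before-after change in the GLDS arm cannot separate a GLDS effect from background treatment, natural course or regression to the mean; only the contrast with placebo can. The sentence that says how effectiveness will be evaluated does not name that contrast.

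**Working it through.** **The plan's own figure.** Section 2.9 arrives at 27.5 per group, rounded to 28, then 30. The last step reproduces: 28/0.95 = 29.5, so 30. The 27.5 cannot be checked, because no control rate is given. It concerns a binary effective rate, so it neither uses nor is changed by the choice of analysis for the scale scores.

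**Inputs from the article.** 30 per arm, 1:1 allocation, and 28 per arm before the dropout allowance. All scales are measured at baseline and week 4.

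**Assumptions (not in the article).** Pre/post correlation r = 0.3, 0.5 or 0.7; equal SDs at both times, scaled to 1; two-sided 0.05.

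**Step 1: variance per patient**

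- Week-4 score alone: 1
- Raw change: 2(1 − r)
- ANCOVA: 1 − r²

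ANCOVA relative to raw change is (1 − r²)/[2(1 − r)] = (1 + r)/2. Relative to the week-4 score it is 1 − r².

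| r | ANCOVA / raw change | 30 per arm is worth | ANCOVA / week-4 score | 30 per arm is worth |
|---|---|---|---|---|
| 0.3 | 0.65 | 30/0.65 = 46 | 0.91 | 30/0.91 = 33 |
| 0.5 | 0.75 | 30/0.75 = 40 | 0.75 | 30/0.75 = 40 |
| 0.7 | 0.85 | 30/0.85 = 35 | 0.51 | 30/0.51 = 59 |

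ANCOVA beats raw change for every r below 1, and the week-4 score for every r other than 0.

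**Step 2: what that does to power.** For an assumed difference of 0.7 SD with 30 per arm:

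| r | Raw change | Week-4 score | ANCOVA |
|---|---|---|---|
| 0.3 | 63% | 77% | 81% |
| 0.5 | 77% | 77% | 88% |
| 0.7 | 94% | 77% | 97% |

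**Step 3: are the unadjusted tests valid?** Simulation with no treatment effect (20,000 trials, 30 per arm, r = 0.3, 0.5, 0.7) gave rejection rates of 4.6% to 5.3% for the week-4 score, raw change, percentage change, the >30% responder split and ANCOVA. The loss is one of efficiency, not of error control.

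**Step 4: a before-after reading with an inert product.** Take 28 per arm, r = 0.5 and a shared improvement of 0.5 SD. The SD of the change is √[2(1 − 0.5)] = 1, so the paired t noncentrality is 0.5 × √28 = 2.65 and the power is 0.723.

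- GLDS arm significant before-after: 72%
- GLDS significant and placebo not: 0.723 × 0.277 = 0.200, about 20%
- Exactly one arm significant, either one: 2 × 0.200 = 40%; half of these are placebo-only results

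Simulation at 30 per arm and r = 0.5 shows how the GLDS-only figure depends on the shared improvement: 15% at 0.2 SD, 23% at 0.3 SD and 19% at 0.5 SD. At 1 SD it is near zero, because both arms are then significant in over 99% of trials.

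**The case against.** **The trial is controlled and the article provides for group comparison.** Section 2.1 calls it randomised and controlled, section 2.13 allows for comparison among groups, and no paired test is named. Comparing index changes may well mean comparing them between arms. This stands. A reader might infer that the plan is to claim efficacy from the GLDS arm alone; the article does not say so. What remains is an ambiguity: the effectiveness sentence names no contrast, and section 2.13 does not say which quantity the groups are compared on. Its pairwise follow-up tests do not settle the matter, since with two arms they add nothing.

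**The percentage index is not shown to be the test variable.** This also stands. A reader might infer that the continuous percentage will be analysed and will lose much power. Section 2.11 uses it to sort patients into response classes and describes no test of it. If it were tested, the loss against ANCOVA would depend on the assumptions: 81% against 78% power in one simulated example (28 per arm, r = 0.5), and gaps of about 11, 5 and 2 points at r = 0.3, 0.5 and 0.7 in another (30 per arm, 0.7 SD). Nor does baseline imbalance go wholly uncorrected: change and percentage change both use the baseline, only imperfectly.

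**A reader might quote 40% as the chance of a misleading result for GLDS.** Half of that is significance in the placebo arm alone. The figure that would favour GLDS is about 20%, and it arises only if within-arm tests are used.

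**Covariates are usually left to the analysis plan, and this is a condensed article.** This is partly right. Silence would be no finding, but the article prints its tests and all are unadjusted, so the point concerns what it states.

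**ANCOVA leaves the sized endpoint alone.** Correct. The effective rate is binary, and the variance ratios apply to the scale scores only.

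**Conclusion.** The point holds as a free improvement, not as an error that invalidates the trial. The named tests keep their 5% level under randomisation but do not use the baseline scores as a covariate. The size depends on r, which the article does not give. Over r = 0.3 to 0.7, ANCOVA variance is 0.65 to 0.85 of that for raw change and 0.91 to 0.51 of that for the week-4 score, assuming equal SDs.

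The second part is a wording risk. If before-after tests were used to judge effectiveness, an inert product would look effective within its own arm in about 72% of trials, and GLDS alone would be significant in about 20%. Both figures assume 28 per arm, r = 0.5 and a shared improvement of 0.5 SD. The article does not commit to such tests; its wording fails to exclude them.

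**What to change.** - In section 2.13, state that for each scale (Clinical Symptom Rating Scale, Phlegm-Blood Stasis Syndrome Scale, Seattle Angina Questionnaire) the week-4 score is compared between arms by ANCOVA, with arm as factor and that scale's baseline score as covariate. Report the adjusted GLDS-minus-placebo difference with its 95% CI.
- In section 2.11, reword the effectiveness sentence so that conclusions rest on between-arm contrasts, and say that within-arm changes are shown descriptively.
- Keep the percentage index to classify responders, and state that the effective rate that sized the trial is compared between arms.

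The cost is a change of wording before the data are unblinded. The scores are already planned, and no visits, patients or change to the sample size are needed.
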